### Statistical Analysis

In this study, we define 3 analysis populations: the full analysis set (FAS), the per-protocol set (PPS), and the safety analysis set (SAS). The FAS includes all patients for whom the primary outcome was obtained. Following the intention-to-treat principle, we will analyze data based on the assigned group in the FAS analysis. The PPS consists of the FAS population, excluding patients who violated eligibility criteria after randomization, had 7 or more contiguous days of nonuse of the iAide2, or took medications affecting sleep. The SAS includes all patients who used the iAide2 at least once after randomization. In the safety analysis using the SAS, we will analyze data based on the intervention actually used by patients, regardless of allocation. The FAS will serve as the primary analysis population, while the PPS will provide supportive results. All safety analyses will be conducted using the SAS.

Patient characteristics will be presented as mean, SD, minimum, 25th percentile, median, 75th percentile, and maximum for continuous variables, and as frequency and proportion for categorical variables.

In the primary analysis, we will compare the change in HbA_1c_ from baseline (E0) to week 12 (E3; or the point of discontinuation, if earlier) between groups using analysis of covariance, with baseline HbA_1c_ (ie, HbA_1c_ at E0) included as a covariate in the FAS. For participants who discontinue the study, the most recent HbA_1c_ measurement before E3 will be used.

We will also conduct 2 subgroup analyses: one based on baseline HbA_1c_ at E0 (<8.5% or ≥8.5%) and the other based on age at initial registration (E0; <65 or ≥65 years). Subgroup analyses of the primary outcome will be performed in each analysis set to assess whether the efficacy of BedTime is consistent across these subgroups.

In the secondary analysis, changes in HbA_1c_ at week 12 (E3) and week 24 (E4) will be analyzed using the same approach as in the primary analysis. The proportion of patients with HbA_1c_ below 7% at E3 and E4 (or at the point of discontinuation, if earlier) will be compared between groups using the Fisher exact test. Changes from baseline in step counts, various laboratory test values, and questionnaire scores at E3 and E4 (or at the point of discontinuation, if earlier) will also be analyzed as key endpoints. Changes in T2D medications, categorized as weakened, unchanged, or strengthened, will be compared between groups using the Cochran-Mantel-Haenszel test. The proportion of newly added medications will be compared between groups using the Fisher exact test. A paired (2-sample) *t* test will be used for within-group comparisons of changes in TPB Questionnaire measurements over weeks 0 (E1), 10 (E2), 12 (E3), and 24 (E4). Changes in TPB Questionnaire and SRB Questionnaire measurements between week 12 (E3) and week 24 (E4) will be compared using a *t* test. A paired *t* test will also be used for within-group comparisons from week 0 (E1) to week 12 (E3) for goal achievement rate, goal increment rate, goal reduction rate, average number of coping strategies implemented per day, and the number of identified barriers.

As an exploratory analysis, we will use linear regression to examine the relationship between the average number of coping strategies implemented per day and improvement in HbA_1c_ within the intervention group. The model will include the average number of coping strategies implemented per day and baseline HbA_1c_ as explanatory variables, with the change in HbA_1c_ as the response variable. Changes from baseline to week 12 (E3) and week 24 (E4) (or the point of discontinuation, if earlier) will be assessed.

We will perform a statistical analysis of safety outcomes by calculating the frequency, number of cases, and percentage of individuals experiencing adverse events during the trial, intervention, and observation periods. For the intervention and observation periods, data will be compiled separately for each group, and the percentages will be compared between groups using the Fisher exact test.

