### Patient Recruitment

Patients will be recruited from 9 medical institutions in Japan (Textbox 1). Attending physicians will conduct recruitment during patients’ regular outpatient consultations. The recruitment period will run from February 8, 2024, to July 30, 2024.

Participating institutions: 11 medical centers in Japan.The University of Tokyo HospitalMitsui Memorial HospitalMeiji Yasuda Life Insurance Company Tokyo HospitalKobe University HospitalAkita University HospitalTokai University HospitalOkayama Saiseikai General HospitalSawaki Internal Medicine and Diabetes ClinicYokota Medical ClinicAikawa Comprehensive Internal Medicine ClinicYokohama Rosai Hospital

To detect a 0.3% difference in the primary outcome (change in HbA_1c_), assuming an SD of 0.41% (the average observed in 2 prior studies [17,61]), and to achieve a 2-sided significance level of .05 with 80% statistical power, the minimum required sample size is 31 patients per group. Considering an estimated dropout rate of approximately 10%, we aim to recruit a total of 70 patients (35 in the intervention group and 35 in the control group).

All participants will receive a comprehensive written and verbal explanation before providing written informed consent. Eligibility screening will be conducted only after consent is obtained. If any findings related to efficacy or safety arise during the trial that may impact patient consent, we will promptly disclose this information to participants and obtain renewed consent.

We will use survey instruments as part of the inclusion and exclusion criteria (Textbox 2). To recruit patients who are both likely to benefit and capable of participating, we will include only those meeting all inclusion criteria (Textbox 3) while ensuring they do not meet any exclusion criteria (Textbox 4), following the methods of a prior study [62]. We anticipate a roughly equal sex distribution and an average participant age in the late 50s. Women undergoing menopausal transition will be included if they meet the study’s criteria.

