We will provisionally register patients who meet the eligibility criteria at E0. At this stage, each participant will receive an actigraph (iAide2) and will be instructed to wear it 24 hours a day, except when bathing, to press the Event button at bedtime, and to record their bedtimes and risetimes in the diary. Patients who fail to press the Event button for 7 or more days or fail to complete the diary for 7 or more days during the run-in period will be excluded to ensure adequate participation. Data collected during the run-in period will be used to confirm eligibility and establish baseline sleep and step counts. We will randomize eligible participants in a 1:1 ratio to either the intervention or control group using covariate-adaptive randomization by minimization to ensure balance across age (<65 and ≥65 years), sex, HbA_1c_ (<8.5% and ≥8.5%), and institution [72]. Random allocation will be conducted via the Internet Data and Information Center for Medical Research cloud, provided by the University Hospital Medical Information Network, an internet-based central randomization system. A research co-investigator will access the University Hospital Medical Information Network Internet Data and Information Center for Medical Research cloud and input the required baseline information. The system will then securely generate the allocation result immediately before assigning each participant to a group. This process ensures that researchers cannot access or predict allocation results in advance, minimizing potential bias.

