E1	Registration, allocation, and beginning of the intervention	Beginning of the intervention	Verify that run-in diary and iAide recording do not cause exclusion Finalize registration and allocation Collect medication status Intervention only: conduct surveys (TPB^i^ Questionnaire, SRB^j^ Questionnaire) Distribute the intervention diary or the control group diary Check for malfunctions or adverse events during run-in
Intervention period	Ongoing measurement	From E1 for 12 weeks	Patients record daily bedtime and risetime, with automated (blinded) measurements of sleep parameters and step count Intervention only: daily feedback, weekly self-set barriers and coping strategies via diary, weekly personalized target bedtime setting via SMS text messages
E2	Ongoing measurement	End of 10 weeks from E1	Intervention only: conduct TPB Questionnaire via diary
E3	End of the intervention	End of 12 weeks from E1	Collect physical data: hemoglobin levels, albumin, uric acid, blood urea nitrogen, estimated glomerular filtration rate, creatinine, fasting blood glucose, HbA_1c_, low-density lipoprotein cholesterol, high-density lipoprotein cholesterol, triglycerides, urine specific gravity, urinary protein, urine albumin-to-creatinine ratio, body weight, and blood pressure measurements Collect medication status Conduct surveys (TTM Sleep Questionnaire, TPB Questionnaire, SRB Questionnaire, PSQI-J) Intervention group: conduct survey (feedback survey) Collect actigraph (iAide2) and intervention period diary Check for malfunctions or adverse events
E4	End of follow-up	End of 24 weeks from E1	Collect physical data: hemoglobin levels, albumin, uric acid, blood urea nitrogen, estimated glomerular filtration rate, creatinine, fasting blood glucose, HbA_1c_, low-density lipoprotein cholesterol, high-density lipoprotein cholesterol, triglycerides, urine specific gravity, urinary protein, urine albumin-to-creatinine ratio, body weight, and blood pressure measurements Collect medication status Conduct surveys (TTM Sleep Questionnaire, TPB Questionnaire, SRB Questionnaire, PSQI-J)

^a^HbA_1c_: hemoglobin A_1c_.

^b^STOP-J: Snoring, Tiredness, Observed Apnea, High Blood Pressure Screen, Japanese version.

^c^ISI-J: Insomnia Severity Index, Japanese version.

^d^IRLSQ-J version 2.2: International Restless Legs Syndrome Study Group Rating Scale, Japanese version.

^e^AUDIT-C-J: Alcohol Use Disorders Identification Test—Consumption, Japanese version.

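### Run-in adverse events are to be reported on a safety set that requires device use after randomisation, so patients excluded before allocation are missing from the run-in figure

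*Protocol article*

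**What the plan says.** The Statistical Analysis section defines the safety analysis set (SAS): "The SAS includes all patients who used the iAide2 at least once after randomization". It makes no exception for any period: "All safety analyses will be conducted using the SAS".

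The last paragraph of that section lists what will be tabulated, including the "percentage of individuals experiencing adverse events during the trial, intervention, and observation periods". It continues: "For the intervention and observation periods, data will be compiled separately for each group". The first of the three periods is thus not split by group.

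Device exposure starts earlier. Under Patient Recruitment, at provisional registration (E0), "each participant will receive an actigraph (iAide2) and will be instructed to wear it 24 hours a day". The pre-allocation exclusions in Textbox 4 then remove anyone with fewer than 7 days of diary entries, Event-button records or valid iAide2 sleep data. Table 4, row E1, schedules the data collection: "Check for malfunctions or adverse events during run-in". Table 1 also lists the adverse-event and malfunction question at E1 for both groups.

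**The concern.** The plan collects run-in adverse events and promises a percentage for that period, but the population assigned to the calculation is fixed by behaviour after the period has ended. Everyone given the device at E0 is exposed during the run-in. Only those who pass the E1 criteria, are randomised and then wear the device again are in the denominator.

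The filter between those two groups is adherence to the device and diary, and adherence can be related to tolerability. If some patients recorded too few days because the wristband bothered them, their events are the ones that drop out. The run-in table would then describe the tolerability of round-the-clock wear only in patients who had already shown they could manage it. The Discussion makes possible integration into standard care conditional on the intervention being shown to be effective and safe, and the wearable is one of its components.

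**Working it through.** **Step 1. Which period is the trial period?** Textbox 4 uses the term for the time in which the pre-allocation recording criteria must be met. Table 5, footnote d, uses it as the baseline for change in sleep measures. The safety paragraph compiles data by group only for the other two periods, as expected if the first precedes allocation. All three uses point to the run-in.

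**Step 2. Who is exposed and who is counted?**

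| Patient | Given iAide2 at E0 | Can be in the SAS |
|---|---|---|
| Excluded at E1 for too few recorded days | Yes | No, never randomised |
| Randomised, never uses the device again | Yes | No |
| Randomised, uses the device at least once afterwards | Yes | Yes |

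Only the third row enters the run-in percentage.

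Who falls in the first row is itself unclear. Textbox 4 excludes for fewer than 7 days recorded. The running text says "Patients who fail to press the Event button for 7 or more days" are excluded (likewise for the diary). In a 14-day run-in, a patient with exactly 7 recorded days passes the Textbox 4 criterion and fails the one in the running text. The two passages must be reconciled.

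**Step 3. Size.** The text gives no count of run-in exclusions or run-in events, so there is no stated figure to reproduce. The only document figure used is the 70 participants, taken here as all belonging to the SAS. Everything else is assumed.

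Let *a* be the number of SAS patients with a run-in event, *m* the number excluded before allocation after receiving the device, and *e* the number of those *m* with an event.

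- Planned figure: *a*/70
- Figure in everyone given the device: (*a* + *e*)/(70 + *m*)
- Difference: (70*e* − *a m*)/[70(70 + *m*)], which is positive only if *e*/*m* > *a*/70

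| *m* | *e* | *a* | SAS figure | All given the device |
|---|---|---|---|---|
| 0 | 0 | any | *a*/70 | *a*/70 (no effect) |
| 1 | 1 | 0 | 0/70 = 0% | 1/71 = 1.4% |
| 3 | 3 | 0 | 0% | 3/73 = 4.1% |
| 5 | 5 | 0 | 0% | 5/75 = 6.7% |
| 10 | 10 | 0 | 0% | 10/80 = 12.5% |
| 10 | 3 | 0 | 0% | 3/80 = 3.8% |
| 3 | 3 | 2 | 2/70 = 2.9% | 5/73 = 6.8% |
| 10 | 10 | 2 | 2.9% | 12/80 = 15.0% |
| 10 | 0 | 2 | 2.9% | 2/80 = 2.5% |

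Rows with *e* = *m* are extremes, because every excluded patient is assumed to have had an event. In the last row the SAS figure is slightly too high. The definitions fix the restriction of the denominator, but not the direction of any error.

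**The case against.** Several points on the other side stand.

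- Two of the three pre-allocation exclusions are plain recording failures (diary, Event button), and the stated purpose is adequate participation. A patient who forgot the diary need not have had any event. A reader might infer that the run-in figure is biased downwards by construction, or that patients are known to have stopped because of harm. The documents say neither.
- Stopping early does not always lead to exclusion. The run-in is nominally 2 weeks and Textbox 4 asks for 7 days, so a patient who stops after that may still be randomised. That patient is in the SAS only on using the device again.
- The effect may be nil. The article reports 70 enrolled and 70 completing observation, and Table 4 labels E0 as enrolment. On that reading nobody was lost in the run-in. Enrolled could equally mean allocated, and the flow diagram is not available here to settle it.
- The run-in precedes allocation, so the comparison of arms in the intervention and observation periods is untouched.

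A reader might also infer that the SAS is wrongly defined after randomisation, because both arms wear the same device and its use does not show exposure to BedTime. The documents do not support that as an error. Membership (device used at least once) and the arm analysed (intervention actually used) are separate rules, and a safety set based on exposure is a defensible choice.

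One objection does not stand: that the run-in denominator is detail an article may leave to the full protocol. The article states which set applies to all safety analyses and which periods are reported, and the two do not fit together.

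**Conclusion.** The point holds in a limited form. Followed as written, the plan computes the run-in adverse-event percentage in a population that cannot contain patients given the iAide2 at E0 but excluded before allocation. This rests on reading the trial period as the run-in, which three places in the article support.

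The figure understates run-in events only if excluded patients had proportionally more of them than retained ones. Under the assumed range of 1 to 10 excluded patients, all with an event and none among the 70 retained, the gap is 1.4 to 12.5 percentage points. With no exclusions it is zero. The text does not say where in that range the trial lies. No efficacy result and no between-group safety result changes. What is affected is any statement on how well the device was tolerated during the run-in.

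**What to change.** In the Statistical Analysis section, give the run-in its own safety denominator: all provisionally registered patients given the iAide2 at E0, including those later excluded before allocation. Report adverse events and device malfunctions in that group, list the reason for each exclusion, and state for how many excluded patients no adverse-event answer was recorded. Keep the SAS as defined for the intervention and observation periods.

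The cost is a change of wording and one extra table. The E1 check is already scheduled, and the article describes the analysis as still under way. Recruitment has ended, so only answers already recorded for excluded patients can be used, and any gaps have to be reported as such. The run-in rate may look slightly less favourable.

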We selected the HbA_1c_ level as our primary outcome, as it is recognized as a global standard for assessing glycemic control and an appropriate indicator of T2D treatment effectiveness [77]. According to the Japan Diabetes Society’s treatment guidelines, patients with T2D should aim to lower their HbA_1c_ level below 7% to prevent complications [78]. Therefore, in addition to analyzing absolute changes in HbA_1c_ levels, we examined the proportion of patients achieving an HbA_1c_ level below 7%. We acknowledge that T2D duration may influence the primary outcome. Although our recruitment process does not explicitly stratify participants by disease duration, this information is collected at registration and will be incorporated into the analysis to account for its potential impact on study outcomes.

In this study, we have chosen a “formidable” control [79], using the same devices as the intervention group. As an initial proof-of-concept study, our goal is to determine whether our specific behavior change intervention is more effective than simply having patients record their bedtime and risetime. Evidence suggests that providing patients with a pedometer can increase their activity levels [80], raising concerns that bedtime and risetime recording in the control group may similarly trigger behavioral changes, potentially making it more challenging to demonstrate the intervention’s superiority statistically. By providing the control group with a diary but withholding the intervention functionality, we have designed the study to offer strong evidence of the intervention’s effectiveness—should it indeed be effective.

Many behavior interventions demonstrate solid short-term gains that later fade [39]. This study includes a 12-week observation period following the intervention to assess whether the benefits persist or diminish. Behavior change maintenance is theorized to result from active, ongoing self-regulation, with habit formation emerging after a period of successfully regulating a new behavior [81]. Our goal is to foster sustainable behavior change, ensuring that the new pattern becomes an enduring habit.

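### The primary ANCOVA leaves out three of the four minimisation factors, which makes it conservative if they are prognostic, and the promised use of diabetes duration belongs to no stated model

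*Protocol article*

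**What the plan says.** Allocation (Protocol article, Patient Recruitment) is 1:1 by minimisation "to ensure balance across age (<65 and ≥65 years), sex, HbA_1c_ (<8.5% and ≥8.5%), and institution".

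The primary analysis (Statistical Analysis) compares change in HbA1c between arms "using analysis of covariance, with baseline HbA_1c_ (ie, HbA_1c_ at E0) included as a covariate in the FAS". The secondary HbA1c analyses at E3 and E4 follow the same approach. Age returns only as a subgroup factor. Sex and institution appear in no described analysis.

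The Discussion accepts that diabetes duration may affect the primary outcome and says that "this information is collected at registration and will be incorporated into the analysis to account for its potential impact on study outcomes". It does not say which analysis, or in what role.

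The running text of Patient Recruitment, like the Abstract, gives 9 institutions. Textbox 1 gives 11 and lists eleven.

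**The concern.** Minimisation makes the arms alike on the chosen factors, so chance imbalance in them contributes less to the variance of the treatment difference. A model without those factors leaves their variance in the residual and computes its standard error as if they had not been balanced. If the factors predict outcome, the reported interval is wider than the true sampling error warrants, the test rejects too rarely under the null, and precision already gained by the allocation is lost. This matters more in a trial of 70 patients than in a large one.

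The duration commitment is a separate matter. Because it has no place among the stated models, a reader of the results could not tell whether an HbA1c model with duration was the one intended.

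Neither point is detail left to an analysis plan that is not shown: the article itself names the primary covariate, and it makes the duration commitment in its own text.

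**Working it through.** **Inputs from the document** (Patient Recruitment): difference 0.3 and SD 0.41 ("To detect a 0.3% difference in the primary outcome (change in HbA_1c_), assuming an SD of 0.41"); two-sided alpha 0.05 and 80% power; "the minimum required sample size is 31 patients per group"; about 10% dropout and 70 patients in total; 9 or 11 institutions.

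**Assumptions, not in the document:** the share R² of the variance left after baseline HbA1c that age, sex and institution explain (0 to 0.30); a minimisation probability of 0.8; and 0.41 taken as the SD after baseline adjustment, although the article gives it for the change itself.

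**Step 1: the plan's own figure.** n per arm = 2 × [0.41 × (1.960 + 0.842) / 0.3]² = 29.3, so 30 by the normal formula. With the t distribution, power is 0.796 at 30 and 0.809 at 31, so 31. Then 31 / 0.9 = 34.4, so 35 per arm and 70 in total. The stated figures reproduce. They assume no covariate gain, so nothing below changes them.

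**Step 2: the limiting case of perfect balance, 31 per arm.**
- Stated model: SE = 0.41 × √(2/31) = 0.104. With 59 degrees of freedom the half-width is 0.208.
- The true sampling SD is 0.104 × √(1 − R²). At R² = 0.3 this is 0.104 × 0.837 = 0.087.
- The adjusted half-width at R² = 0.3 is then 0.175, a ratio of 0.84. The stated model's type I error is about 1.7%, by a normal approximation that returns 4.5% at R² = 0.

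Minimisation over 9 or 11 small sites does not reach perfect balance, so the real effect is smaller.

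**Step 3: simulation.** 70 patients were minimised on the four factors and analysed by least squares, with 3000 runs per setting. R² was split equally between age, sex and site. Each cell gives 9 sites / 11 sites. Width is relative to the stated model.

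| R² | Type I error, stated | Type I error, + age, sex, site | Width, + age, sex | Width, + age, sex, site |
|---|---|---|---|---|
| 0 | 0.046 / 0.053 | 0.044 / 0.052 | 1.00 / 1.00 | 1.04 / 1.05 |
| 0.1 | 0.042 / 0.048 | 0.054 / 0.051 | 0.97 / 0.97 | 0.98 / 1.00 |
| 0.2 | 0.037 / 0.029 | 0.055 / 0.049 | 0.93 / 0.93 | 0.93 / 0.94 |
| 0.3 | 0.026 / 0.026 | 0.046 / 0.054 | 0.89 / 0.89 | 0.87 / 0.88 |

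Power for a difference of 0.3:

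| R² | Stated | + age, sex | + age, sex, site |
|---|---|---|---|
| 0 | 0.858 / 0.847 | 0.857 / 0.847 | 0.837 / 0.810 |
| 0.1 | 0.868 / 0.866 | 0.877 / 0.881 | 0.864 / 0.860 |
| 0.2 | 0.872 / 0.880 | 0.902 / 0.909 | 0.897 / 0.893 |
| 0.3 | 0.886 / 0.890 | 0.930 / 0.925 | 0.932 / 0.927 |

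The Monte Carlo standard error of a type I rate near 5% is √(0.05 × 0.95 / 3000) = 0.004, so small differences between cells are noise. A second simulation (11 sites, 5000 runs) gave 0.051, 0.038, 0.035 and 0.029 for the stated model and 0.053, 0.044, 0.045 and 0.055 for the fully adjusted one. Its average model SE was 0.098, against true sampling SDs of 0.094, 0.091 and 0.087 at R² = 0.1, 0.2 and 0.3.

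At R² = 0.3 the full interval width falls from 0.39 to 0.34-0.35 HbA1c points. That is 11-13% narrower; put the other way, the stated interval is 12-15% wider (1/0.894 = 1.12; 1/0.872 = 1.15).

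**Step 4: duration.** The covariate list in Statistical Analysis has one entry, baseline HbA1c. The exploratory regression adds only coping strategies. Neither subgroup analysis uses duration. The Discussion's commitment therefore matches nothing in that section.

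**The case against.** The stated model is valid. Its error is on the safe side, and its simulated power with 70 analysed is about 85-89% in every scenario, above the 80% target. The article reports 70 participants completing observation, so the dropout allowance was hardly needed. The gain from adjustment rests on an assumed R²: at 0 there is none and fixed site terms widen the interval by 4-5%, and at 0.1 full adjustment leaves the width almost unchanged. The article also says that analysis is underway, so replacing a clearly stated primary model now could itself be a data-driven choice. All of this stands. It limits the size of the point and governs how the change may be made, but it does not remove the mismatch between allocation and model.

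Two stronger readings are tempting and unsupported. One is that the trial's error bars are too wide as a matter of fact. The article gives no figure for how well age, sex or institution predict HbA1c change, so this can only be conditional. The other is that the primary model is stated in two different ways. Statistical Analysis states it once. The Discussion mentions neither the primary analysis nor a covariate, and a sensitivity model or subgroup would fit its wording equally well. It is a commitment without a place, not a second primary model.

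**Conclusion.** The point holds in conditional form. Three of the four minimisation factors are missing from the primary model. The cost runs from nothing, if they do not predict HbA1c change, to a type I error of about 2.6-3% and an interval that adjustment would narrow by 11-13%, if they explain 30% of the residual variance. At that upper end, power for 0.3 is 88-89% as stated and about 93% with full adjustment. The omission loses precision and does not inflate false positives. Age and sex are almost free to add (width ratio 1.00 at R² = 0), whereas 8-10 fixed site terms are not.

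The sizes rest on the assumed R², its equal split between the three factors in the tabulated runs, the assumed minimisation probability and the use of 0.41 as a residual SD. Only fixed site terms were simulated, so no figure here describes a random intercept. The unplaced duration commitment is a matter of wording to reconcile. It does leave open which HbA1c model a reader should take as planned.

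**What to change.** 1. Add age and sex to the primary model alongside continuous baseline HbA1c, and state the form in which age enters. The simulation used the two categories of the minimisation.
2. Include institution as a random intercept, or put it in a named sensitivity model. Settle the 9 versus 11 institution count first, since it sets the number of sites.
3. Use the same covariates for HbA1c at E4.
4. Assign diabetes duration to one named sensitivity analysis, and make Statistical Analysis and the Discussion agree.
5. Record the change before any comparison by arm is seen. The Results section says both that analysis is underway and that a data review will precede it, so the record should state which applied. If a comparison has been seen, keep the baseline-only model as primary and report the adjusted models as labelled sensitivity analyses.

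The cost is a few sentences and two degrees of freedom for age and sex. Age, sex and institution are already recorded for allocation, and disease duration is collected at registration, so no new data and no change in sample size are needed.
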